## Abstract

**Background:**

Child maltreatment has severe short-and long-term consequences for children’s health, development, and wellbeing. Despite the provision of child protection education programs in many countries, few have been rigorously evaluated to determine their effectiveness. We describe the design of a multi-site gold standard evaluation of an Australian school-based child protection education program. The intervention has been developed by a not-for-profit agency and comprises 5 1-h sessions delivered to first grade students (aged 5–6 years) in their regular classrooms. It incorporates common attributes of effective programs identified in the literature, and aligns with the Australian education curriculum.

**Methods/Design:**

A three-site cluster randomised controlled trial (RCT) of Learn to be safe with Emmy and friends™ will be conducted with children in approximately 72 first grade classrooms in 24 Queensland primary (elementary) schools from three state regions, over a period of 2 years. Entire schools will be randomised, using a computer generated list of random numbers, to intervention and wait-list control conditions, to prevent contamination effects across students and classes. Data will be collected at baseline (pre-assessment), immediately after the intervention (post-assessment), and at 6-, 12-, and 18-months (follow-up assessments). Outcome assessors will be blinded to group membership. Primary outcomes assessed are children’s knowledge of program concepts; intentions to use program knowledge, skills, and help-seeking strategies; actual use of program material in a simulated situation; and anxiety arising from program participation. Secondary outcomes include a parent discussion monitor, parent observations of their children’s use of program materials, satisfaction with the program, and parental stress. A process evaluation will be conducted concurrently to assess program performance.

**Discussion:**

This RCT addresses shortcomings in previous studies and methodologically extends research in this area by randomising at school-level to prevent cross-learning between conditions; providing longer-term outcome assessment than any previous study; examining the degree to which parents/guardians discuss intervention content with children at home; assessing potential moderating/mediating effects of family and child demographic variables; testing an in-vivo measure to assess children’s ability to discriminate safe/unsafe situations and disclose to trusted adults; and testing enhancements to existing measures to establish greater internal consistency.

**Trial registration:**

Australian and New Zealand Clinical Trials Register (ACTRN12615000917538). Registered (02/09/2015).

## Background

Child maltreatment is a serious and widespread problem affecting children around the world [1, 2]. The term child maltreatment refers to one or more of 4 major subtypes: physical abuse, emotional (or psychological) abuse, sexual abuse, and neglect. Child maltreatment can involve acts of omission or commission by parents, caregivers, or community members (e.g. teachers, clergy) and may result in death, serious injury, or exploitation [3, 4]. Epidemiological monitoring reveals it is associated with a variety of specific negative outcomes for children, including higher levels of mental illness, poverty, greater engagement with crime, and physical, emotional, mental and social maladjustment across the entire developmental trajectory [5–8].

One way to help children to learn about and safeguard themselves from maltreatment is through school-based child protection education programs, which were first implemented in the USA in the 1980s [9, 10]. Also known as child abuse prevention, child assault prevention, child safety, personal safety, and protective behaviours programs [9–13], these typically focus on teaching severalcore concepts, including how to recognise safe and unsafe situations, how to react when approached, and how to identify safe adults to speak with about unsafe situations [14]. A major benefit of child protection education programs is that, unlike programs focusing solely on one type of harm (i.e. bullying, physical violence, sexual harassment), they equip children with knowledge and skills that may be generalised to recognise, react to and report multiple types of harm and risk situations.

Despite the wide uptake of child protection education programs in countries as diverse as Germany, Hong Kong, Taiwan, Turkey, and the United States [15], systematic reviews and meta-analyses highlight that very few highly rigorous program evaluations exist [15–19]. Indeed, it has been identified that few evaluations have used control groups and randomised designs, whilst fewer still track outcomes for more than 6 months to examine the long-term effectiveness of these programs. There have also been concerns regarding the measures utilised to evaluate outcomes. For example, recommendations for future research designs include the need to measure: a) primary or targeted program outcomes such as self-protective skills, behaviour change, abuse disclosures;b)multiple program outcomes including knowledge, intentions, skills,and program satisfaction,within the one sample; and c) potential negative impacts such as increased fear or anxiety.

This study extends an earlier successful Australian study of a specific child protection education program, *Learn to Be Safe with Emmy*™ [20]. This was a quasi-experimental study in which classrooms were randomised to conditions (program and waitlist); with the waitlist comparison group receiving the program after they completed post-test measures (5 weeks after administration of baseline measures). In this study, a total of 245 first grade students (aged 5–6 years) participated in the *Learn to Be Safe with Emmy*™ program, recruited from five primary (elementary) schools on the Gold Coast, Queensland. The study demonstrated the program was effective in increasing participants’ self-protective knowledge and skills, and their intentions to respond in a safe manner to unsafe situations including hypothetical situations with risks of bullying, abuse and sexual assault, without increasing or decreasing child anxiety.

The current study will extend on Dale et al. [20] in six ways. It will: (i) use a larger sample, with schools from a broader range of demographic areas; (ii) randomise at school-level to prevent cross-learning between conditions; (iii) provide a 6-month follow-up for the waitlist control condition, and 12- and 18-month follow-ups for the intervention condition; (iv) examine the degree to which parents/guardians discuss intervention content with children at home; (v) develop and utilise an in-vivo measure to assess children’s ability to discriminate safe/unsafe situations and disclose their experience to trusted adults; and (vi) enhance the intentions to respond measure by asking about both safe and unsafe situations to test if safety responses (i.e. telling an adult) were used appropriately according to the level of perceived risk.

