### Aims

The aim of this study is to conduct an empirical assessment, using a cluster randomised-controlled trial [21], of key outcomes of the *Learn to be safe with Emmy and friends*™ program. Specifically, the current study will test the following five hypotheses:When compared to children in the waitlist condition for the same period, children in the intervention condition will show the following changes from pre-test to post-test:significantly greater increase in knowledge of interpersonal safetysignificantly greater ability to distinguish between safe and unsafe situationssignificantly greater intention to engage in safe responses to unsafe situationssignificantly greater confidence to take appropriate action in unsafe situations
When compared to parents/guardians of children in the waitlist condition for the same period, parents/guardians of children in the intervention condition will report significantly greater increases in their child’s knowledge of interpersonal safety and use of self-protective skills.Post-intervention, children in the intervention condition will:refuse a simulated in vivo lure by an unfamiliar adult at post-intervention at a higher rate than children in the waitlist condition.disclose the presence of an unfamiliar adult i) earlier; and ii) at a higher rate, than children in the waitlist condition.
Children’s post-intervention knowledge of interpersonal safety will be positively correlated with both behavioural intentions, application of self-protective skills, and disclosure.Children’s anxiety scores will not change from pre-intervention to post-intervention.

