#### Observed Protective Behaviours Test (OPBT)

This will be administered to children in the control and intervention conditions at either post-test evaluation or the six-month evaluation. A structured two-part in vivo behavioural situation has been developed by the first author expressly for this study and will be used to test children’s ability to implement the safety skills learned during *Learn to be safe with Emmy and friends*™. Part 1 will measure recognition of unsafe situations and theapplication of relevant safety skills. Children will be presented with a simulated unsafe situation enacted by an unfamiliar confederate. In the script for the unsafe situation after greeting the child, the interviewer will leave the room under the pretext of making a telephone call [30]. During the interviewer’s absence,a confederate will enter the room and ask the child to leave with them. The confederate will then remember that they have forgotten a bag and leave, asking the child to keep their presence a secret and dropping a pen to the floor as they leave. The manipulation will take approximately 1 min with the interviewer returning within 30 s of the confederate exiting and resuming the interview.

Part 2 will test children’s disclosure of the unsafe situation. In this, children will be presented with 6 prompts to disclose the presence of the confederate (e.g., “You probably didn’t notice if the pen was in the room before, did you?”). At the end of the interview, prior to administering the anxiety measure the confederate will return and the secret will be revealed. This will provide an opportunity for the interviewer to model disclosure of the unsafe situation with the child and engage in debriefing. The OPBTis based on behavioural skills training and measures used by Johnson et al. [31, 32] and Gunby et al. [33] in evaluations of children’s personal safety skills, as well as the secret-keeping scenario and seven point secret-keeping scale created by Dunkerley and Dalenberg [30].

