### Planned analyses

Mixed factorial analyses of variance (ANOVAs) will be used to examine the effectiveness of the program for primary outcomes. Analyses will be conducted to assess differences between the intervention and waitlist control conditions over time using 2 (Group: intervention, waitlist-control) x 3 (Time: T1, T2, T3) mixed ANOVAs. Primary or target outcomes include children’s knowledge of program concepts, intentions to use program knowledge, skills, and help-seeking strategies, and anxiety as a result of program participation. T-tests will be conducted to examine the difference between groups in use of program skills and disclosure during the simulated situation conducted at T2 and T3.

Following the 6-month follow-up of the children who received the program, data will be analysed to assess stability of improvement in the treatment group from post to, 6-, 12- and 18-month follow-up. One-way ANOVAs will also be conducted for these variables for the intervention group across the five time points (T1, T2, T3 and T4, T5).

Hierarchical linear modelling [37] will be used to examine any effects of the hierarchical structure of the study design. If there are hierarchical effects, this analysis will be used to account for influences of classroom (level 2) and school level effects (level 3), while examining the effects of condition (Emmy/waitlist) and within student changes over time. Regression will be used to test the mediation analyses and to examine any effects of moderators (e.g. demographic variables, parental stress, dose–response) to determine which factors may differentiate intervention effects. Intent-to-treat analyses will also be conducted to account for potential effects of differential drop-out.

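### The in-vivo test is described as measuring discrimination between safe and unsafe situations, but it stages only an unsafe one, so refusal cannot be told apart from general wariness of unfamiliar adults

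*Protocol article*

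**What the plan says.** The fifth of six extensions over the previous study, listed in the Background, is to "develop and utilise an in-vivo measure to assess children’s ability to discriminate safe/unsafe situations and disclose their experience to trusted adults". The Discussion paragraph of the Abstract says the same: "testing an in-vivo measure to assess children’s ability to discriminate safe/unsafe situations and disclose to trusted adults".

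The section on the OPBT then describes the procedure:

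- The stimulus: "Children will be presented with a simulated unsafe situation enacted by an unfamiliar confederate".
- Part 1: "Part 1 will measure recognition of unsafe situations", together with the use of safety skills.
- Part 2: "Part 2 will test children’s disclosure of the unsafe situation", by means of six prompts from the interviewer.
- Timing: it is "administered to children in the control and intervention conditions at either post-test evaluation or the six-month evaluation".

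The Aims attach two kinds of hypothesis to this test. One is that intervention children will "refuse a simulated in vivo lure by an unfamiliar adult at post-intervention at a higher rate than children in the waitlist condition". The other is that they will disclose the unfamiliar adult earlier and more often. Planned analyses provides t-tests for the "difference between groups in use of program skills and disclosure during the simulated situation conducted at T2 and T3".

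Safe scenarios appear in one child measure only, the APBT-R. It has two safe and four unsafe scenarios, told as verbal narratives with line drawings. The child judges each of the six as safe or not, and correct answers are summed to a Total Risk Accuracy score.

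**The concern.** The article gives the OPBT a property that its procedure does not supply. To show that a child discriminates, one must see the child respond differently to a safe and to an unsafe situation. The OPBT shows only the response to the unsafe one.

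This matters because the Abstract names actual use of programme material in a simulated situation as a primary outcome. If the intervention arm refuses the lure more often, there are two possible explanations: better discrimination, or a general shift towards refusing unfamiliar adults. The programme aims at the first, since Session 2 in Table 1 teaches children to tell safe from unsafe situations, including ones that feel unsafe but are not. The second would be an unwanted effect, and Part 1 would count it as success.

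**Working it through.** The documents give no figure for this point, so there is nothing to reproduce. The check sets the stated purpose beside the procedure and then asks what the data can identify.

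**Step 1. Purpose against procedure.**

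| Place in the article | Safe in-vivo condition? |
|---|---|
| Abstract (Discussion) and Background, item (v) | Implied: discrimination of safe from unsafe |
| OPBT, Part 1 | None: one unsafe situation |
| OPBT, Part 2 | None: disclosure of that same situation |
| Aims, in-vivo hypotheses | None: refusal of the lure, disclosure |
| Planned analyses | None: skill use and disclosure in the simulated situation |

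The OPBT section speaks of a script for the unsafe situation. That does not establish a second, safe script, because both parts of the two-part test are defined on the unsafe event.

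**Step 2. What Part 1 identifies.** Write discrimination as

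D = P(refuse | unsafe) − P(refuse | safe).

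Part 1 observes the first term only. A child who refuses every unfamiliar adult has D = 1 − 1 = 0. A perfect discriminator has D = 1 − 0 = 1. Both refuse the lure.

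**Step 3. Illustration at group level.** All rates here are assumed; none comes from the article.

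| | P(refuse, unsafe) | P(refuse, safe) | D |
|---|---|---|---|
| Control | 0.50 | 0.20 | 0.30 |
| Programme A | 0.70 | 0.20 | 0.50 |
| Programme B | 0.70 | 0.40 | 0.30 |

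The OPBT shows 50% against 70% for both programmes. Discrimination improves by 20 points under A and by 0 under B. A larger sample does not help, because the missing term is never observed. Other assumed rates change the numbers but not this conclusion.

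**Step 4. What the APBT-R adds.** Calling every scenario unsafe scores 4/6; perfect discrimination scores 6/6. The Total Risk Accuracy score therefore separates these two extremes. Between them the sum is less clear. Three of four unsafe plus two of two safe gives 5/6, and four of four unsafe plus one of two safe also gives 5/6.

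More generally, let u be the chance of calling an unsafe scenario unsafe, and s the chance of calling a safe one unsafe. Then

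expected score = 4u + 2(1 − s).

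If both u and s rise by d, the score changes by 4d − 2d = +2d, although u − s is unchanged. Using the assumed rates of Step 3 for u and s:

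- Control: 4(0.50) + 2(0.80) = 3.6
- Programme A: 4(0.70) + 2(0.80) = 4.4
- Programme B: 4(0.70) + 2(0.60) = 4.0

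The summed score rises under B as well, by 2 × 0.20 = 0.4 points. Safe-scenario accuracy on its own shows the difference: 80% under A, 60% under B.

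**The case against.** The strongest reply is that this is a mismatch of wording and not a failed aim. The phrase stands in a Background list and in the Abstract, not in the Aims. The in-vivo hypotheses are refusal and disclosure, and the OPBT can test both. The hypothesis on distinguishing safe from unsafe situations is not tied to the OPBT, and the APBT-R serves it. The Background also says that safe scenarios were added to the intentions measure to see whether safety responses are used appropriately, and anxiety is monitored with the RCMAS-2. All of this stands.

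It rules out several stronger readings that a reader might infer:

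- *That a stated hypothesis cannot be tested.* None of those in the Aims depends on a safe in-vivo condition.
- *That wariness of all adults would pass the whole OPBT.* Part 2 depends on confiding in the interviewer, which blanket wariness does not explain. The point is confined to Part 1 and to unfamiliar adults.
- *That the trial as a whole is blind to over-caution.* The APBT-R collects answers to safe scenarios. The RCMAS-2 measures anxiety, which is not the same thing.
- *That Part 1 cannot measure recognition of an unsafe situation.* The article does not show how Part 1 is coded, so this cannot be judged.
- *That results will be misreported as discrimination.* The Aims and Planned analyses speak of refusal, skill use and disclosure.

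The reply does not restore the claim itself. The APBT-R uses narratives and drawings, so it cannot support a statement about in-vivo discrimination. Nor is the contradiction a matter of condensation: the article describes the procedure in enough detail to conflict with its own summary of it.

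**Conclusion.** The concern holds in a limited form. The Abstract and Background say that the in-vivo measure assesses discrimination between safe and unsafe situations. As described, the OPBT does not, because it contains no safe situation, and Part 1 refusal cannot separate discrimination from general wariness of unfamiliar adults.

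No trial figure changes: sample size, hypotheses and planned tests are untouched. What changes is the conclusion that a positive OPBT result permits, which is more refusal and more disclosure of one staged unsafe lure. Conclusions about discrimination rest on the APBT-R and reach only hypothetical scenarios. Its summed score, with four unsafe and two safe items, can itself rise through a general shift towards calling things unsafe.

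The conclusion assumes that the OPBT section describes the whole procedure and that no safe in-vivo scenario exists elsewhere. The rates in the illustration are assumed; the argument does not depend on them.

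**What to change.** 1. In the Abstract (Discussion) and in item (v) of the Background list, describe the OPBT as measuring children's response to, and disclosure of, one staged unsafe lure by an unfamiliar adult. Remove the statement that it assesses discrimination.
2. State that conclusions on discriminating safe from unsafe situations come from the APBT-R only, and apply to hypothetical scenarios.
3. Report APBT-R accuracy by arm separately for the two safe and the four unsafe scenarios, beside the OPBT refusal rate. State in advance that higher refusal together with lower safe-scenario accuracy in the intervention arm will be read as general wariness.

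The cost is a change of wording and one table from data already planned; no new procedure and no further children are needed. There are two downsides. The in-vivo claim becomes narrower. With two safe items, each child's safe-scenario score can only be 0, 1 or 2, so the table helps interpretation but does not replace an in-vivo comparison.

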### Aims

The aim of this study is to conduct an empirical assessment, using a cluster randomised-controlled trial [21], of key outcomes of the *Learn to be safe with Emmy and friends*™ program. Specifically, the current study will test the following five hypotheses:When compared to children in the waitlist condition for the same period, children in the intervention condition will show the following changes from pre-test to post-test:significantly greater increase in knowledge of interpersonal safetysignificantly greater ability to distinguish between safe and unsafe situationssignificantly greater intention to engage in safe responses to unsafe situationssignificantly greater confidence to take appropriate action in unsafe situations
When compared to parents/guardians of children in the waitlist condition for the same period, parents/guardians of children in the intervention condition will report significantly greater increases in their child’s knowledge of interpersonal safety and use of self-protective skills.Post-intervention, children in the intervention condition will:refuse a simulated in vivo lure by an unfamiliar adult at post-intervention at a higher rate than children in the waitlist condition.disclose the presence of an unfamiliar adult i) earlier; and ii) at a higher rate, than children in the waitlist condition.
Children’s post-intervention knowledge of interpersonal safety will be positively correlated with both behavioural intentions, application of self-protective skills, and disclosure.Children’s anxiety scores will not change from pre-intervention to post-intervention.

## Methods/Design

The Human Research Ethics Committees at Griffith University (GU Ref No: PSY/48/14/HREC) approved this study, as did the Research Committee at the Department of Education and Training, Queensland. It is also registered with the Australian and New Zealand Clinical Trials Register (ACTRN12615000917538) and has received Australian Research Council funding under the Linkage Projects scheme (ID: LP130100304) in a partnership between Griffith University, James Cook University, Queensland University of Technology and the not-for-profit organisation, Act for Kids.

The study consists of a three-site cluster randomised control trial using a waitlist-control group. The unit of randomisation will be the school. The unit of analysis will be individual children; however the nesting effects of classes, schools, and site location will be taken into account through hierarchical modelling. Data from parents/guardians about immediate child outcomes will be paired with the respective child data. The main outcome evaluation will be supplemented by a process evaluation using fidelity data from facilitators, session auditors, and satisfaction surveys completed by parents/guardians and teachers.

